### Study setting

Participants will be recruited from five sites within the Queensland Palliative Care Research Group (QPCRG). These five sites have been chosen from the QPCRG as they have an established research team including research support systems within Palliative Care and have previous experience in trial participation in this setting. It is anticipated that this will be predominately an outpatient study, with these sites having the ability to access this participant population from their established clinic service.

All participants will be given standard palliative care according to the local practice of the recruiting centre [12]. They will continue all current medications including opioids, antiemetics, sedatives and specific anti-cancer therapy (including chemotherapy, immunotherapy and radiotherapy).

### Study participants

Patients who meet the inclusion criteria will have an advanced histologically proven cancer diagnosis (metastatic or locally advanced), be known to and be receiving palliative care at the recruiting centre and have an ESAS Total Symptom Distress Score (TSDS) of ≥ 10/90 for cancer-related symptoms and at least one individual ESAS score ≥ 3/10 [13]. They must have a Performance Status AKPS (Australia-modified Karnofsky Scale score) of ≥ 30/100 [14], be aged ≥ 25 years, have a negative THC urine test at commencement of trial and be able to tolerate oral medications and must be either English-speaking or have an interpreter available.

Female participants must have a negative pregnancy urine test at eligibility (only if of reproductive potential) and agree to avoid pregnancy during the study and 12 weeks following the last dose of the study drug. Males must agree to avoid fathering a child and to not donate sperm during the study and for at least 12 weeks following the last dose of the study drug. Further to this, the Alcohol, Smoking and Substance Involvement Screening Test (ASSIST) will be completed [15]. It is designed to determine whether harmful substances are being used and go undetected or become worse. The assessment is comprised of 8 questions assessing, tobacco, alcohol, cocaine, amphetamine-type stimulants, sedatives, hallucinogens, opiates and ‘other drugs’.

Exclusion criteria include a history of hypersensitivity to any cannabinoid, unstable untreated cardiovascular disease, severe hepatic impairment (total bilirubin ≥ 1.5 times the upper limit of the normal range), aspartate aminotransferase (AST) and alanine aminotransferase (ALT) ≥ 3.0 times the upper limit of the normal range (subjects with liver metastasis may have an AST and ALT of ≥ 5.0 times the upper limit of normal), severe renal impairment (eGFR ≤ 20 mL/min/1.73 m^2^), a history of psychiatric disorders (severe depression or anxiety, personality disorder, psychosis, schizophrenia, first-degree relative with schizophrenia and/or suicidal ideation), cognitive impairment (St Louis University Mental Status examination (SLUMS) ≤ 20/30) [16] and a known substance use disorder (Alcohol, Smoking and Substance Involvement Screening Test (ASSIST) examination scoring > 27) for any substance.

Potential participants will be excluded if they have a history suggesting that drug diversion may be a risk for them or their family/carers, have participated in a trial of a new clinical entity within the last 28 days or had treatment with a new specific anti-cancer agent (chemotherapy, targeted or hormonal therapy) or radiation within the last 7 days.

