### Assessments

Participants will receive 2 times/weekly research nurse phone calls in the first 2 weeks and outpatient clinic medical review visits at days 7, 14, 21 and 28, with outcome measures recorded at these points.

Symptom burden will be measured using the Edmonton Symptom Assessment Scale (ESAS). Confirmed documented disease status will be assessed at days 14 and 28, where applicable.

A routine haematology and biochemistry screen including liver function tests will be taken at eligibility/baseline assessment. Blood for C-reactive protein (CRP) as a basic test of inflammation will be taken at baseline, day 14 and day 28. All consenting participants will have a urine test to confirm nil recent use of THC-related products as a pre-screen. Female participants of childbearing potential will have a urine test to determine pregnancy. At day 14, a urine sample will be collected and stored (frozen) until the completion and un-blinding of the study. Samples will be stored on site and transported to central storage in batches over the course of the study. These samples will be for post-trial analysis for evidence of no THC product use during the trial.

Participants will be contacted at day 56 (+ 4 weeks post last dose) for the purposes of safety follow-up and recording of post-study cannabinoid use. Date of death will be recorded for all participants up to the census point. This protocol has been written in accordance with the Standard Protocol Items: Recommendations for Interventional Trials (SPIRIT) (Table 1).

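### The liver-metastasis exception to the AST/ALT exclusion points the wrong way: read literally, it admits patients with both enzymes at 5.0 x ULN or above and excludes those with both at 3.0 to below 5.0

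*Protocol article*

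**What the plan says.** All of the following is in the protocol article, Methods, unless noted.

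- **Setting of the rule.** The sentence in Study participants is a list of exclusions. It opens with "Exclusion criteria include a history of hypersensitivity to any cannabinoid".
- **General transaminase rule.** One item is "aspartate aminotransferase (AST) and alanine aminotransferase (ALT") ≥ "3.0 times the upper limit of the normal range". The two enzymes are joined by *and*.
- **Exception.** The bracket attached to that item says "subjects with liver metastasis may have an AST and ALT of" ≥ "5.0 times the upper limit of normal".
- **Other limits for the same patients.** Bilirubin has its own exclusion, "severe hepatic impairment (total bilirubin" ≥ 1.5 x ULN). Further exclusions follow in the next paragraph, which begins "Potential participants will be excluded if they have a history suggesting that drug diversion may be a risk".
- **Liver tests.** Assessments states: "A routine haematology and biochemistry screen including liver function tests will be taken at eligibility/baseline assessment".

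No other part of the article gives an AST or ALT limit for patients with liver metastasis.

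**The concern.** An exception to an exclusion normally relaxes it by a stated amount. Here the verb grants permission while the sign sets a lower bound. The values permitted are therefore the highest ones, and the moderate elevations that such an exception exists to admit remain excluded.

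What is at stake is who may receive study drug. Metastatic cancer is an eligible diagnosis, so the exception covers a foreseeable group. Participants may titrate up to 30 mg/30 mg a day and take study drug for up to 28 days (Intervention). In the text that is shown, liver function tests are stated only at eligibility/baseline, while CRP is repeated at days 14 and 28. The schedule table is not shown, so later liver tests may exist. An entry threshold of this kind should be readable without inference. Literal use would also turn away patients with moderate elevations whom the trial evidently meant to include.

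**Working it through.** The article gives no figure to reproduce, so this is a check of logic.

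**Inputs** (Study participants): general exclusion at ≥ 3.0 x ULN; liver-metastasis permission at ≥ 5.0 x ULN; enzymes joined by *and*.

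**Population:** a patient with liver metastasis, bilirubin below 1.5 x ULN and no other exclusion. Anyone else excluded is out under every reading.

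**Step 1: both enzymes at the same level.**

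- Literal rule: excluded if the value is ≥ 3.0 and not ≥ 5.0.
- Intended rule: excluded if the value is ≥ 5.0.

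| Both enzymes (x ULN) | Literal | Intended |
|---|---|---|
| 2 | eligible | eligible |
| 3, 4, 4.9 | excluded | eligible |
| 5, 8, 20 | eligible | excluded |

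The two rules disagree at every value from 3.0 upwards.

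**Step 2: the enzymes may differ.** Three bands for each enzyme (< 3.0, 3.0 to < 5.0, ≥ 5.0) give 3 x 3 = 9 combinations. The word *and* can be taken in three ways:

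- **A.** Both enzymes must be raised to exclude. Literal: eligible unless both ≥ 3.0, but re-admitted if both ≥ 5.0. Intended: excluded if both ≥ 5.0.
- **B.** Either enzyme excludes, and the exception needs both ≥ 5.0. Literal: eligible if both < 3.0 or both ≥ 5.0. Intended: excluded if either ≥ 5.0.
- **C.** Either enzyme excludes, and the exception applies to each enzyme separately. Literal: eligible if each enzyme is < 3.0 or ≥ 5.0. Intended: as in B.

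Each cell shows literal / intended; *in* means eligible, *out* means excluded.

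| Bands | Combinations | A | B | C |
|---|---|---|---|---|
| both < 3.0 | 1 | in / in | in / in | in / in |
| one < 3.0, one 3.0 to < 5.0 | 2 | in / in | out / in | out / in |
| one < 3.0, one ≥ 5.0 | 2 | in / in | out / out | in / out |
| both 3.0 to < 5.0 | 1 | out / in | out / in | out / in |
| one 3.0 to < 5.0, one ≥ 5.0 | 2 | out / in | out / out | out / out |
| both ≥ 5.0 | 1 | in / out | in / out | in / out |

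Conflicts:

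- A: 1 + 2 + 1 = 4 of 9
- B: 2 + 1 + 1 = 4 of 9
- C: 2 + 2 + 1 + 1 = 6 of 9
- Under all three: 1 + 1 = 2 of 9, namely both at 3.0 to < 5.0 and both at ≥ 5.0

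Only the last count is independent of how *and* is read.

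**Step 3: is it a printing fault?** The same sentence prints ≤ correctly for eGFR and for SLUMS, so a general loss of that sign is not the explanation.

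**The case against.** The strongest reply is that nobody would be misled. Almost every number in the list is the value that excludes: bilirubin ≥ 1.5, AST/ALT ≥ 3.0, eGFR ≤ 20, SLUMS ≤ 20, ASSIST > 27. On that pattern the bracket simply moves the excluding value from 3.0 to 5.0. A rule that shuts out 4 x ULN and admits 20 x ULN is clinically absurd, and a screening clinician is unlikely to apply it. This stands, and it is why the point is minor. It does not make the sentence correct: staff who follow the text and staff who follow the evident intent would apply opposite rules.

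A second reply concerns reach. Recruitment began on 9 September 2019 under protocol version 1.3 (Trial status), about ten months before the article appeared on 6 July 2020. Sites therefore did not begin screening from the article. This stands too. A reader might infer that patients with grossly raised transaminases were enrolled or dosed. The article does not support that, because version 1.3 and the site eligibility form are not shown.

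A reader might also infer that liver-metastasis patients face no hepatic limit at all. That goes too far: the bilirubin exclusion still applies to them, although it does not cap AST or ALT. The unlimited admission needs liver metastasis, both enzymes at ≥ 5.0 x ULN (on readings A and B), bilirubin below 1.5 x ULN and no other exclusion. Adverse events are also reviewed by the DSMB at least every 6 months.

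**Conclusion.** Wrong as written, and minor. For otherwise eligible patients with liver metastasis, the sentence gives the reverse of the evident intent in two cases: both enzymes at 3.0 to below 5.0 x ULN, and both at 5.0 x ULN or above, where no ceiling is set.

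The larger counts of 4 or 6 of 9 should not be taken as the size of the problem. Each depends on one reading of *and*, which the article does not settle. All of these are counts of combinations, not of patients; how many participants fall in them is unknown.

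The conclusion rests on two assumptions: that the sentence is read literally, and that the intent was a threshold raised from 3.0 to 5.0 x ULN. Power, the primary outcome and its analysis do not depend on this criterion's wording.

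**What to change.** 1. The clinical lead first decides whether one raised enzyme is enough to exclude. The order matters. If the direction alone is corrected and *and* is kept in its both-enzymes sense, a liver-metastasis patient with AST 20 x and ALT 4 x ULN becomes eligible. The present literal text excludes that patient, since both values are ≥ 3.0 and they are not both ≥ 5.0.
2. Restate the exception as a raised exclusion threshold. If either enzyme suffices: *AST or ALT ≥ 3.0 x ULN (≥ 5.0 x ULN in subjects with liver metastasis)*. If both are required, say so explicitly, with the same two thresholds.
3. Check protocol version 1.3 and the site eligibility form. If they are correct, correct the article only. If they carry the same wording, correct them, notify sites, and check enrolled liver-metastasis participants against the baseline liver tests already taken.

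The cost is one clinical decision and a one-line correction to the article. Only if the wording reached version 1.3 or the site form is there more to do: a one-line change there, a site memo and a look-back through existing results, with no new data collection.

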### Consent process

The process for obtaining consent for this study will be exchanging information between the study staff and potential participants and any other person the participant wishes to include in the discussion. A participant information sheet (PICF) will be provided in written form and will be used as the basis for the discussion. This will cover the purpose, expected procedures, participant requirements, risks, benefits, burdens and side effects that are expected or possible during the study. Participants are specifically informed that due to the nature of this medication and current laws in Queensland, you will NOT be able to drive or operate heavy machinery whilst taking the medication. Potential participants will be given the opportunity (in time and physical capacity) to consider the study and formulate any questions. All questions will be addressed and answered fully. An actual time point for consent will not be specified as this will be determined by the person’s physical condition. The consent form is to be completed by trained study team members in accordance with the requirements of the approving ethics committee. The form is to be signed and dated by the participant.

### Assessments

Participants will receive 2 times/weekly research nurse phone calls in the first 2 weeks and outpatient clinic medical review visits at days 7, 14, 21 and 28, with outcome measures recorded at these points.

Symptom burden will be measured using the Edmonton Symptom Assessment Scale (ESAS). Confirmed documented disease status will be assessed at days 14 and 28, where applicable.

A routine haematology and biochemistry screen including liver function tests will be taken at eligibility/baseline assessment. Blood for C-reactive protein (CRP) as a basic test of inflammation will be taken at baseline, day 14 and day 28. All consenting participants will have a urine test to confirm nil recent use of THC-related products as a pre-screen. Female participants of childbearing potential will have a urine test to determine pregnancy. At day 14, a urine sample will be collected and stored (frozen) until the completion and un-blinding of the study. Samples will be stored on site and transported to central storage in batches over the course of the study. These samples will be for post-trial analysis for evidence of no THC product use during the trial.

Participants will be contacted at day 56 (+ 4 weeks post last dose) for the purposes of safety follow-up and recording of post-study cannabinoid use. Date of death will be recorded for all participants up to the census point. This protocol has been written in accordance with the Standard Protocol Items: Recommendations for Interventional Trials (SPIRIT) (Table 1).

**Table 1 Tab1:**
[figure not shown]
SPIRIT figure—study schedule

### Outcomes and assessment tools

The primary outcome is the change from baseline of total ESAS TSDS at day 14.

The ESAS is a 9-item inventory rated on an 11-point scale anchored at 0 (no problem) to 10 (worst problem). It assesses both physical and psychological symptoms, plus general wellbeing. It has been validated in the assessment of symptoms in cancer patients [13].

Secondary outcomes include:
Patient-determined effective dose of THC/CBD formulation, defined as the dose that achieves symptom relief with acceptable side effects.ESAS TSDS at days 7, 21 and 28.Physical and emotional ESAS scores at each time point.
Physical scores will be measured by the Australia-modified Karnofsky Performance Status (AKPS) and Resource Utilisation Groups-Activities of Daily Living Scale (RUG-ADL). The AKPS is a validated variant of the Karnofsky Performance Status. The Australian version can be applied to both in- and outpatients and is sensitive to changes in function over time [14]. The RUG-ADL is an instrument developed for the measurement of nursing dependency. The ADL scale measures patients’ needs for assistance in activities of daily living (eating, bed mobility, transferring and toileting) [17].Individual symptom scores (descriptive analysis only).Oral morphine equivalent (OME), average use at baseline and weekly.Patient Global Impression of Change (PGIC), days 7, 14, 21 and 28.
This is a subjective measure of symptom change completed by the patients themselves [18].Clinical Global Impressions (CGI) Scale, days 7, 14, 21 and 28.
This is a subjective measure of symptom change completed by the investigating clinician [18].The Depression, Anxiety, Stress Scale (DASS-21) score baseline and days 14 and 28.
DASS-21 is a self-reported 21-item scale, 7 questions per sub-item questionnaire measuring depression, anxiety and stress. The DASS-21 will be used for assessment at baseline (day 0) and days 14 and 28 [19].EORTC score QoL baseline and days 14 and 28 [20].This is a QoL measure found valid for use in a wide variety of cancer populations. To reduce patient burden, we will use the 15-question subset commonly used for the palliative care population.NCI common terminology for adverse events V4.03, days 2, 4, 7, 9, 11, 14, 16, 18, 21, 23, 25 and 28 [21]
The NCI CTCAE is a severity grading system for adverse events. Adverse events relate to an unfavourable or unintended sign, symptom or disease temporarily associated with a medical treatment or a procedure which may not be related to the medical treatment or procedure. The CTCAE has a grading of 1 (mild) to 5 (death). The known common adverse events associated with cannabinoids are confusion, somnolence, paranoia, anxiety, mood changes, psychosis, hypertension, tachycardia, hyperhidrosis, nausea, vomiting and abdominal pain [21].

The study will assess adverse events (AE) and serious adverse events (SAE) using the criteria of the NCI CTCAE V4.0 [21]. The known common AEs associated with THC/CBD will be specifically addressed at each time point. Finally, a detailed concurrent medication list is to be updated and recorded at baseline (day 0) and days 7, 14, 21 and 28. This is to include over-the-counter medications, prescribed medications and complementary medication.

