### Intervention

Cannabinoid oils, supplied by LG Pharma, will be used in this study. The decision to use oils was based on a number of factors including product availability, ability to access ongoing supplies, ability to produce matched placebo, regulations surrounding the production and transport of cannabinoid products and cost.

Arm 1 of the trial consists of THC/CBD 10 mg/10 mg/mL oral solution (LG Pharma Pty Ltd) with a dose range of 2.5 mg/2.5 mg–30 mg/30 mg/day and arm 2 a matching placebo oral oil solution. Participants are asked to take daily doses as per dosing schedule instructions. The study drug is to commence on the day of baseline assessment, continuing for a maximum of 28 days.

The cannabinoid oils and placebo will be dispensed in identical 50-mL bottles containing a sufficient quantity of oil. Bottles are to be stored at room temperature (25 °C) until used and stored away from light. The product will be dispensed from bottles with a wadded child-resistant cap. Participants will be given replacement bottles to complete the study as required. Participants will be educated on how to administer daily doses using supplied 1-mL syringes appropriate for the dose. The participant will complete a daily dosing schedule diary at home to record medication taken. Cannabinoid oil that has been allocated to a participant and not used will be returned to the research nurse/research officer and destroyed by the local pharmacy as per pharmacy guidelines.

Dose titration will be confirmed following regular consultation. Each participant will be advised to increase their dose according to a schedule every 2 days until they are satisfied with their symptom improvement or they experience unacceptable side effects. Dose titration downwards will also be allowed, in consultation with research staff. The participant in collaboration with research staff will define the dose level at which they will continue until the primary outcome point (14 days). Participants will then be given the option of remaining on the blinded oil solution for a further 2 weeks (28 days total) for continuing assessment of efficacy and adverse events (continue final dose if perceived to be of benefit and tolerated). Assessment at 28 days following 14 days of stable dose is a secondary end point.

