An interim analysis will be performed after 50% participants have completed 14 days of the trial. The analysis will be performed by an independent biostatistician blinded for the treatment allocation and reported to the investigators and the Data Safety Monitoring Board (DSMB). The purpose of the interim analysis is primarily to monitor and ensure safety of participants rather than evidence of such benefit that early stopping of the trial is justified. AEs and SAEs will be stratified by type and severity. The frequency of AEs and SAEs will be compared between treatment groups using chi-square tests and logistic regression if indicated to adjust for any baseline differences between groups. Differences in baseline characteristics are not anticipated, as the randomisation process should ensure that the patient groups are similar at baseline. However, as the numbers at interim analysis will be relatively smaller, it is possible that differences may arise by chance. All baseline characteristics will be assessed and any imbalance addressed in the analysis.

If the interim analysis shows a significant difference, the investigators and DSMB will be un-blinded to the study groups and make any stopping decision on the basis of the nature of any AEs and/or SAEs and ethical grounds, as well as consideration of any statistical differences between the groups. Grounds for stopping on evidence of clear benefit will be considered. The Peto approach will be taken with symmetric stopping boundaries at *p* = 0.001.

A detailed statistical analysis plan will be prepared and ratified by the DSMB. Stata, SAS (SAS® version 9.4 software (SAS Institute Inc., Cary, NC, USA)) or R (R Core Team (2017). R: A language and environment for statistical computing. R Foundation for Statistical Computing, Vienna, Austria. URL https://www.R-project.org/) will be used for analysis and all code recorded for the purposes of ensuring reproducible research.

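### The listed CTCAE time points start at day 2 with no pre-dose grade, and the text does not limit adverse events to new or worsened ones, so symptoms present at entry can count as events in both arms

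*Protocol article*

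**What the plan says.** All references are to the Methods of the protocol article.

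- **Outcomes and assessment tools** gives the adverse-event schedule as "NCI common terminology for adverse events V4.03, days 2, 4, 7, 9, 11, 14, 16, 18, 21, 23, 25 and 28". That is twelve time points, none before dosing. In the same list, opioid use, DASS-21 and the EORTC score each name baseline.
- **Intervention** states: "The study drug is to commence on the day of baseline assessment, continuing for a maximum of 28 days". The first listed grade therefore falls after treatment has started.
- **Outcomes and assessment tools** names the known events as "confusion, somnolence, paranoia, anxiety, mood changes, psychosis, hypertension, tachycardia, hyperhidrosis, nausea, vomiting and abdominal pain" and adds: "The known common AEs associated with THC/CBD will be specifically addressed at each time point". Its definition of an adverse event includes one "which may not be related to the medical treatment or procedure" and sets no condition that the event be new or worse than before treatment.
- **Study participants** requires that patients "have an ESAS Total Symptom Distress Score (TSDS) of ≥ 10/90 for cancer-related symptoms and at least one individual ESAS score ≥ 3/10".
- **Statistical analysis and sample size**, in the interim-analysis paragraph, says: "The frequency of AEs and SAEs will be compared between treatment groups using chi-square tests". Logistic regression is available to adjust for baseline differences between groups, and events are to be stratified by type and severity.

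**The concern.** Patients enter this trial because they have symptoms, and some of the solicited events are symptoms of that kind. A participant with standing nausea who is asked about nausea on day 2 will report it. Without a CTCAE grade from before the first dose, that report cannot be separated, on the CTCAE scale, from nausea that began or worsened on treatment.

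Randomisation makes such standing symptoms about equally frequent in the two arms. Counting them adds the same background to both and shrinks the contrast. The planned logistic regression does not remove this: it is offered for chance imbalance between groups, not for symptoms present equally in both.

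At stake is the sensitivity of the interim comparison, whose stated purpose is mainly safety and which can lead to unblinding and a stopping decision. A later analysis plan can define which events count, but it cannot recover a grade that was not collected.

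**Working it through.** **The plan's own figure.** The only sample-size figure concerns the primary efficacy outcome: a difference of 6, SD 11.6, two-sided 5%, 80% power. The normal approximation gives n = 2 × (1.960 + 0.842)² × 11.6² / 6² = 58.7, so 59 per arm; the t-test solution is 59.65, so 60. Then 60 / 0.80 = 75 randomised per arm. The stated figure reproduces and this point does not affect it. It supplies the 75 per arm used below.

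**Inputs for the illustration.** The documents give no adverse-event rates, so these are assumptions:
- r, the new-onset risk among those free of the symptom at day 0: 10% on placebo and 30% on active (risk ratio 3.0).
- q, the share with the symptom at day 0, equal in both arms: 0% to 60%.
- Test: two-sided 5%. The article gives a stopping boundary of p = 0.001 but no separate level for the adverse-event tests. A stricter level would lower every power figure below.

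**Formulas.** If every grade of 1 or more after day 0 counts, the recorded frequency is q + (1 − q) × r. The risk difference is then (1 − q) × (0.30 − 0.10). If only new events count, over all randomised, the frequency is (1 − q) × r. Power is for a two-proportion z test, with pooled variance under the null and unpooled under the alternative.

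Example, q = 40%: placebo 0.40 + 0.60 × 0.10 = 0.46; active 0.40 + 0.60 × 0.30 = 0.58. The difference is 0.12 and the risk ratio 0.58 / 0.46 = 1.26.

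| q | Recorded, placebo v active | Risk ratio | Power, all counted | Power, new events over all randomised | Power, only those symptom-free at day 0 |
|---|---|---|---|---|---|
| 0% | 10% v 30% | 3.0 | 0.872 | 0.872 | 0.872 |
| 20% | 28% v 44% | 1.57 | 0.533 | 0.767 | 0.789 |
| 40% | 46% v 58% | 1.26 | 0.311 | 0.620 | 0.665 |
| 60% | 64% v 72% | 1.125 | 0.181 | 0.438 | 0.490 |

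**Other assumed onset rates**, 75 per arm, q = 40%:
- 20% v 40% (true risk ratio 2.0): recorded 52% v 64%, risk ratio 1.23; power 0.318 with all counted, 0.481 with new events only.
- 15% v 30% (true risk ratio 2.0): recorded 49% v 58%, risk ratio 1.18; power 0.195 and 0.363.

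**At the interim.** Half of 150 is 75, about 37 per arm. With 10% v 30% and q = 40%, power is 0.175 with all counted and 0.353 with new events only. With nobody symptomatic at entry it would be 0.578.

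**Limits of the model.** It treats every pre-existing symptom as an event and allows no worsening. The new-events columns therefore leave out worsened events, which the proposed definition would also count.

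**The case against.** The strongest reply is that the absence of a day-0 grade is not established. The SPIRIT study schedule (Table 1) is not shown and may mark one. Silence in the outcome list proves little: the same list gives the ESAS total at days 7, 21 and 28 without baseline, although baseline ESAS is needed for both eligibility and the primary outcome. This stands. A reader might infer that the trial takes no pre-dose grade; the documents support only that the time points written in the text include none.

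Second, counting only treatment-emergent events is a rule commonly left to the full protocol or analysis plan, and the article says a detailed plan will follow. This also stands for the definition taken alone. It does not dispose of the data-collection schedule, which the article fixes. The adverse-event definition does refer to an association in time with treatment, but a standing symptom graded on day 2 also coincides with treatment.

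Third, baseline information exists. ESAS, DASS-21 and SLUMS cover part of the gap, and exclusions for psychosis, severe depression or anxiety, and cognitive impairment should make several of the twelve events uncommon at entry. So the point concerns some solicited events, not all. What baseline data there are, however, are not CTCAE grades, and the article does not say they will serve as such.

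Fourth, stratification by severity would limit masking of higher-grade events by standing mild symptoms, and the DSMB reviews all events at least six-monthly without depending on a chi-square test. Both are right. A reader might infer that the plan hides drug harm; the documents do not support that.

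**Conclusion.** The point holds in limited form. As written, the CTCAE schedule starts after dosing, the solicited list includes symptoms plausible at entry, and the text does not restrict events to new or worsened ones. The any-grade comparison can therefore be pulled towards no difference.

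This is conditional on grades from day 2 being counted as they stand, which the text permits but does not state. The direction is towards the null; with equal prevalence in both arms no false difference arises. The risk difference shrinks by the factor (1 − q), for example from 20 to 12 percentage points at 40% prevalence. Every rate behind the risk ratios and power figures is assumed, so they show the mechanism and not the trial's actual loss. Nor should the remedy be oversold: in the main illustration at 40% prevalence, counting new events only brings power at 75 per arm from 31% to 62%, not back to 87%, and at the interim it stays low at about 35%.

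The change is worth making because it is cheap and because a missing pre-dose grade cannot be reconstructed reliably afterwards.

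**What to change.** 1. In Outcomes and assessment tools, add day 0, before the first dose, to the CTCAE time points for the solicited events. If the SPIRIT schedule already has such a check, align the text with it.
2. In Statistical analysis and sample size, or in the analysis plan, base the interim and final arm comparisons of these events on those that are new since day 0 or of higher grade than at day 0.
3. Recruitment began in September 2019. If no pre-dose grade has been taken so far, state how participants already dosed will be handled, since their grades cannot be recovered reliably.

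The cost is one checklist at the existing baseline visit, a few minutes for the participant, and a wording change. No extra visit or staff is needed.
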